### Sample size calculation

Sample size estimations were based on the distribution of outcomes in MISTIE III,^12^ and on data from the DIST pilot study.^19^ We assumed a distribution of mRS in controls as follows: mRS 0: 0%; mRS 1: 5%; mRS 2: 15%; mRS 3: 20%; mRS 4: 25%; mRS 5: 15%; mRS 6: 20%, and a favourable treatment effect with a common odds ratio of 1.49, corresponding to an absolute risk difference of mRS 0-3 of 11%. In a Monte Carlo simulation with 5000 runs, we computed the proportion of positive trials for a given sample size. This yielded a sample size of 800, providing a 90% power to detect a true treatment effect, with a 2-sided alpha of 0.05. In the analysis, we will use covariate adjustment, under the assumption that this reduces the sample size by 25%.^26^ Therefore, the final sample size will consist of 600 patients, 300 for each treatment group.

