### Randomisation

Eligible patients will be randomised by local site personnel via a secure web-based internet system. Patients will be allocated in a 1:1 ratio to either minimally invasive endoscopy-guided surgery in addition to standard medical management (intervention group), or to standard medical management alone (control group), using permuted blocks with random block sizes of 10 or 20 stratified by neurosurgical centre. It will not be possible to view the treatment allocation before the patient is randomised. Due to the nature of the intervention, both patient and local site personnel cannot be blinded for the assigned treatment.

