### Deferred consent procedure

Patients will be enrolled using a deferred consent procedure in accordance with the Medical Research Involving Human Subjects Act (WMO).^21^ Written informed consent to continue participation in the study will be obtained from the patient or their representative by trained research personnel, as early as deemed appropriate and reasonable after randomisation (control group) or intervention (intervention group). In patients allocated to the intervention group, we will ask the patient or their representative for consent for the surgical treatment according to common clinical practice for any procedure. Patients who have indicated, as part of advanced care planning, that they do not want to undergo any surgical treatment will not be enrolled. When a representative has provided consent and the patient regains decision-making capacity, we will ask the patient for written consent at that time. If a patient has died before deferred consent has been obtained, the legal representative will be informed about trial participation. Patients or representatives who do not consent will be asked for permission to use routinely collected data and materials. If patients or their representatives object to the use of their data, their data will be registered in an anonymized registry to obtain data on in-hospital rebleeding occurrence and in-hospital mortality for the purpose of safety analyses. All other study information will be completely erased from the patient’s study record.

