### Statistical analysis

The primary analyses will be performed according to the intention-to-treat principle. Baseline data by treatment allocation will be reported with standard statistical procedures. Missing values for baseline characteristics and outcomes will be reported. For the analyses, missing baseline characteristics and outcomes will be imputed using multiple imputation.

The primary effect parameter will be reported as a common odds ratio, estimated with ordinal logistic regression, which represents the shift across the 7-category mRS measured at 180 days. The treatment effect estimate will be adjusted for neurosurgical centre and known prognostic variables: age, pre-stroke mRS, time from symptom onset to randomisation, systolic blood pressure on admission, stroke severity (NIHSS), ICH volume, presence of intraventricular haemorrhage and antiplatelet or oral anticoagulant use immediately before stroke onset. Adjusted and unadjusted estimates with corresponding 95% CIs will be reported. The adjusted analysis with multiple imputation will be considered the primary analysis. In addition, we will perform a per-protocol and as-treated analysis.

Secondary effect parameters will be analysed using linear, logistic or ordinal regression analyses as appropriate, applying the same adjustment variables as for the primary outcome.

The effect of the intervention on the mRS will be analysed in pre-specified subgroups determined by the following variables: tertiles of age; sex; location of ICH (deep vs lobar); tertiles of systolic blood pressure at baseline; tertiles of NIHSS at baseline; tertiles of ICH volume; tertiles of time from symptom onset to randomisation; presence of CTA spot sign and prior use of antiplatelet agents or oral anticoagulants.

For the cost-effectiveness analysis, costs and quality-adjusted life years will be calculated in both groups over the 12-month follow-up period. We will perform a model-based economic evaluation to estimate the lifetime cost-effectiveness of the intervention.

Further details will be provided in a separate statistical analysis plan.

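### The 600 enrolled patients are exactly 75% of 800, so the stated 90% power is reached only if no 180-day outcome information is lost

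*Protocol article*

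**What the plan says.** The article's section on sample size calculation gives the derivation in three steps. A simulation under a common odds ratio of 1.49 is run; "This yielded a sample size of 800", "providing a 90% power to detect a true treatment effect, with a 2-sided alpha of 0.05". Covariate adjustment is then assumed to save 25%. The conclusion follows directly: "Therefore, the final sample size will consist of 600 patients, 300 for each treatment group". The abstract's study design paragraph describes the six hundred as patients to be enrolled.

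Two other sections describe how outcome information can be lost after enrolment.

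- **Deferred consent procedure.** Consent is sought after randomisation (control group) or after the intervention (intervention group). Patients or representatives who decline are first asked whether routinely collected data may be used. If they object to use of the data, in-hospital rebleeding and in-hospital mortality go to an anonymised registry, and "All other study information will be completely erased from the patient’s study record".
- **Statistical analysis.** "For the analyses, missing baseline characteristics and outcomes will be imputed using multiple imputation". The adjusted analysis with imputation is the primary one.

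No expected rate of erasure or of missing 180-day mRS is given, and no replacement of such patients is described.

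**The concern.** The power figure and the patient count refer to different sets of people. The 90% applies to 600 patients with full outcome information; the 600 counts people enrolled, before anyone has been asked for consent. In a deferred-consent trial, some erasure after randomisation is a foreseeable result of the design. An erased patient has neither covariates nor a 180-day mRS, so imputation has nothing to work from. A patient with a missing mRS stays in the analysis but contributes less than an observed outcome would.

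What is at stake is the accuracy of a headline figure. Readers of a neutral result will rely on the stated power to judge what the trial could have detected, and that figure currently assumes zero loss.

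**Working it through.** **Inputs, all from the article.** Two-sided alpha 0.05; power 90%; common odds ratio 1.49; control mRS distribution 0, 5, 15, 20, 25, 15 and 20% for scores 0 to 6; 1:1 allocation; 800 before and 600 after the assumed 25% saving. **Assumed here:** the loss rate *d*, because the article gives none.

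**Step 1: reproduce the 800.** Applying an odds ratio of 1.49 to the control distribution gives 0, 7.27, 19.87, 22.69, 23.62, 12.18 and 14.37% in the surgery arm. Whitehead's proportional-odds formula is

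N = 12 (z₀.₉₇₅ + z₀.₉₀)² / [ (ln OR)² (1 − Σ p̄³) ],

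where p̄ is the mean of the two arms in each category. With Σ p̄³ ≈ 0.0372 and ln 1.49 = 0.3988:

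N = 12 × 3.2415² / (0.1590 × 0.9628) ≈ 824.

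This is 2.9% above the stated 800. Power at 800 is 89.2% by the formula and 88.8% in a simulation of 40,000 runs (score test with ties). The 800 is therefore reproduced to within reasonable tolerance, using complete outcomes. Had the simulation contained an allowance for loss, complete-data power at 800 would lie clearly above 90%, and it does not.

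**Step 2: look for an allowance between 800 and 600.** 800 × (1 − 0.25) = 600 exactly. The covariate saving accounts for the whole step.

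**Step 3: power if a fraction *d* of the 600 contributes nothing.** To avoid importing the small difference in step 1, the calculation starts from the protocol's own 90% at 600 analysed. With information proportional to the number analysed,

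power = Φ[ (1.960 + 1.282) √(1 − d) − 1.960 ].

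| Assumed loss *d* | Analysed, 600(1 − d) | Φ argument | Power |
|---|---|---|---|
| 0% | 600 | 1.282 | 90.0% |
| 2% | 588 | 1.249 | 89.4% |
| 5% | 570 | 1.199 | 88.5% |
| 10% | 540 | 1.115 | 86.8% |
| 15% | 510 | 1.029 | 84.8% |

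Power stays within 2 points of 90% up to a loss of about 6.5%. The table treats a missing mRS as a complete loss, keeps the 25% covariate saving as assumed, and takes losses to be spread evenly over the arms.

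**The case against.** The case on the other side has four parts.

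1. **No loss rate is given, so no shortfall can be asserted.** This stands. A reader might infer that the trial does not deliver 90% power. The article does not support that; it supports only that 90% requires zero loss.
2. **Erasure and missing mRS are different losses.** This stands. Missing outcomes are imputed within the primary analysis, and the day-6 NIHSS and the mRS at 90 and 365 days could inform the imputation. Known deaths are observed outcomes (mRS 6, assumed for 20% of controls), which limits how much can be missing. The table is therefore an upper bound on the damage for this component. For erased records nothing is recoverable.
3. **Refusing consent is not the same as leaving the analysis.** This stands. A reader might infer that every refusal costs power, but only an objection to use of the data leads to erasure.
4. **A condensed article may leave a replacement rule to the full protocol.** This stands in part. If erased patients are replaced there, that component disappears, though missing mRS remains. But the article does set out its derivation from 800 to 600, and that derivation leaves no room for an allowance.

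Two further inferences should be resisted. One is that the 800 is itself too small. A formula or simulated value of 88.8 to 89.2% is too close to 90% to show a deficit: the plan's 5000 runs carry a standard error of √(0.9 × 0.1 / 5000) ≈ 0.4 points, and raising the odds ratio from 1.49 to 1.50 brings simulated power at 800 to 89.9%. The other is that non-adherence lowers power further. Nothing in the article shows that 1.49 is anything other than the effect expected under intention to treat.

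**Conclusion.** The point holds in a limited form. The calculation from 800 to 600 contains no allowance for erased records or missing 180-day mRS, the 600 counts enrolled patients, and the article itself provides for both kinds of loss. The stated 90% is therefore the power with no information lost, and the calculation has no spare margin to absorb any loss.

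The size is modest: at worst about 1.5 points at 5% loss, 3 points at 10% and 5 points at 15%. These figures rest on assumed rates, on loss being complete, and on the protocol's own 90% at 600 analysed. This is a correction to a headline figure; it does not show that the trial is underpowered.

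**What to change.** In the sample size section, state that 600 counts enrolled patients and that the 90% assumes complete 180-day outcomes. Then restate the power for the number expected to have usable outcomes, giving erasure and missing mRS separately. For example, it would be about 88.5% if 5% of enrolled patients contributed no outcome information.

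The rates need not be guessed. With 235 patients enrolled by October 2025, the proportion of records erased, and the proportion without a 180-day mRS among those who have passed that visit, can be reported pooled over arms without revealing any treatment comparison. If the full protocol replaces erased patients, one sentence saying so would settle that component.

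The cost is a few sentences and a slightly less favourable stated power. No extra patients and no change to the design or analysis are required.

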### Trial status

Patient recruitment started in November 2022 and is expected to finish in July 2027. Status of enrolment can be followed at www.dutch-ich.nl (October 2025: *n* = 235).

## Discussion

DIST is a multicentre randomised trial designed to evaluate whether minimally invasive endoscopy-guided surgery performed within 8 hours of symptom onset, in addition to standard medical management, improves functional outcome after 6 months, compared to standard medical management alone in patients with spontaneous supratentorial ICH. Secondary outcomes include safety, technical efficacy, quality of life and cost-effectiveness.

In the recently updated Cochrane review on surgery for spontaneous supratentorial ICH, low-certainty evidence suggested that minimally invasive surgery may increase the chance of good functional outcome.^8^ The effect on mortality was supported by moderate-certainty evidence, whereas the effect on health-related QoL was very uncertain.^8^ Most included studies had high risk of bias and pooled estimates were often imprecise, underscoring the need for high-quality, adequately powered studies to guide clinical practice.

In addition to DIST, several other ongoing randomised trials aim to address this evidence gap,^8^ including EMINENT-ICH (NCT05681988), EVACUATE (NCT04434807), NESICH (NCT05539859) and REACH (NCT06870812). These trials differ in inclusion criteria, timing of surgery and technique of the intervention.

In ENRICH and MISTIE III, only patients with haematoma volumes greater than 30 mL were included. Multiple ongoing studies have now adopted lower thresholds—10 mL in DIST, 20 mL in EVACUATE, EMINENT-ICH and REACH and 25 mL in NESICH—reflecting the hypothesis that minimally invasive surgery may also benefit patients with smaller haematomas, as accumulating evidence demonstrates that minimally invasive surgery can be performed safely. DIST also has broad inclusion criteria with regard to age and clinical condition, in contrast to some other studies, to increase generalisability.

Another distinguishing feature of DIST is the early time window for surgery—within 8 hours of symptom onset—shared only with EVACUATE. Other studies allow intervention up to 24–72 hours. Observational data suggested that haematoma removal may be most effective when performed early, with a 5% increase in the odds of achieving a good functional outcome for each hour surgery started earlier.^27^ Nonetheless, the optimal timing of surgery remains uncertain and warrants further investigation.

A potential advantage of endoscopy-guided evacuation over other minimally invasive approaches is that it permits direct visualisation of residual haematoma and management of active bleeding, including coagulation of focal bleeding points and management of diffuse bleeding through irrigation.^28^ This facilitates effective removal of the haematoma and may result in lower rebleeding rates compared to other minimally invasive approaches. Effective haematoma removal is critical, as multiple studies have demonstrated that lower residual volume is associated with better functional outcome.^29^^,^^30^ Therefore, the DIST protocol includes an NCCT immediately after surgery, with the option to return to the operating room in case of substantial residual haematoma. Currently, it is unclear whether 1 technique is superior to the other with regard to safety and effectiveness. In DIST, participating neurosurgeons must meet credentialing requirements and adhere to a detailed surgical protocol (Supplemental material) to optimise safety and minimise variability.

Completion of all ongoing studies is essential to provide evidence on whether, when, how and in which patients minimally invasive surgery may improve functional outcome. Ultimately, an individual patient data meta-analysis will provide a more granular understanding of treatment effect modifiers and inform personalised treatment strategies. A protocol for this meta-analysis is currently being developed.

In conclusion, DIST is designed to provide robust, high-quality evidence on the effect of minimally invasive endoscopy-guided surgery performed within 8 hours of symptom onset in patients with spontaneous supratentorial ICH. Its results will contribute much-needed new data on the efficacy of haematoma evacuation in this devastating disease, and may guide future clinical decision-making and trial design.
